**11. Risk Assessment whether Expedited Review is Suitable**

| 11.1 | Will study incur extra clinical intervention(s) to subjects? | | | | NO |
| --- | --- | --- | --- | --- | --- |
| 11.2 | Will study impose additional risk to subjects? | | | | NO |
| 11.3 | Will study raise sensitive / important privacy concerns? | | | | NO |
| 11.4 | Will the study involve the following vulnerable subjects? | | | |  |
| 11.4.1 | - Foetuses in Uteri/ non-viable foetuses / abortus | | | | NO |
| 11.4.2 | - Infants (age 0 to ＜1) | | | | NO |
| 11.4.3 | - Children (age 1 to ＜13) | | | | NO |
| 11.4.4 | - Adolescents (age 13 to ＜18) | | | | NO |
| 11.4.5 | - Pregnant / lactating women | | | | NO |
| 11.4.6 | - Persons related unequally to investigators, e.g. student, employee | | | | NO |
| 11.4.7 | - Special population, e.g. prisoner, mentally / cognitively disabled | | | | NO |
| 11.4.8 | - Others: | NO | Specify if yes: |  | |
| 11.5 | Are there any special precautions to protect the interest of vulnerable subjects? | | | | |
|  | In the course of treatment, when patients with adverse reactions, it will get timely medical assistance. According to the patient informed consent, waive part of medical expenses. | | | | |

**12. Study Design and Methodology**

| 12.1 | Study design: | | Prospective ﹡; and Randomized controlled trial ﹡ | | | | | | | |
| --- | --- | --- | --- | --- | --- | --- | --- | --- | --- | --- |
|  | If others, specify: | |  | | | | | | | |
| 12.1.1 | Methods of assignment: | | | Randomization | | | | | | |
| 12.1.2 | Control: | | | Concurrent control (cohort) | | | | | | |
| 12.1.3 | Degree of masking: | | | Single-blinded | | | | | | |
| 12.1.4 | Group assignment: | | | Parallel | | | | | | |
| 12.1.5 | Phase of study: | | | Phase Ⅱ | | | | | | |
| **For PhaseⅠStudy, please complete the “Supplementary Information Sheet for PhaseⅠStudy ”.** | | | | | | | | | | |
| 12.2 | Disease group (*choose the most appropriate one*) | | | | | ENT system | | | | |
| 12.2.1 | Key conditions under study *(e.g. asthma; DM etc)* | | | | | Nasopharyngeal carcinoma; SMART-IMRT; PET-CT; chemoradiotherapy | | | | |
| 12.3 | Study article (Please put “NA” on the field of “Generic name” if nor applicable) | | | | | | | | | |
| Article | Type﹡ | Generic name | | | Duration of exposure | | Dosage | Route of administration | | Was it produced under GMP? |
| 1 | Radiotherapy | SMART-IMRT;PET/CT | | | 7 Week(s) | | 77Gy | Others | | N/A |
| 2 | Radiotherapy | SMART-IMRT; CT | | | 7 Week(s) | | 70Gy | Others | | N/A |
|  |  |  | | |  | |  |  | |  |
|  |  |  | | |  | |  |  | |  |
| Control | Radiotherapy | IMRT; CT | | | 7 Week(s) | | 70Gy | Others | | N/A |
|  | | | | | | | | | | |
| 12.4 | Will an application of clinical trial certificate be made? | | | | | Yes | | | | |
| 12.5 | Has a PhaseⅠstudy been done? | | | | | Yes (for all study articles) | | | | |
| 12.6 | Number of extra visits / admissions on top of usual care: | | | | | | | | | |
| 10-20 patients in each group. | | | | | | | | | |
| 12.7 | Will any of the study interventions / procedures be performed by persons other than the investigators, and if so by whom and where? | | | | | | | | | |
| Block randomisation was by a computer generated random number list prepared by an investigator with no clinical involvement in the trial. We stratified by admission for an oncology related procedure. After the research nurse had obtained the patient’s consent, she telephoned a contact who was independent of the recruitment process for allocation consignment. | | | | | | | | | |
| 12.8 | Will biological samples or date be stored for future use? | | | | | | | | NO | |
| 12.8.1 | If yes, give details and explain how consent will be obtained : | | | | | | | | | |
|  |  | | | | | | | | | |

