**6. Milestones**

| 6.1 | Proposed study start date: | 2 / 2009 (mm / yyyy) ﹡ |
| --- | --- | --- |
| 6.2 | Proposed study end date or date of last follow-up of all recruited subjects, whichever is later: | 4 / 2014 (mm / yyyy) ﹡ |
| 6.3 | Expected final report date to Cluster REC: | 4 / 2014 (mm / yyyy) ﹡ |

**7. Brief Summary of Study** (＜500 words, use language that can be understood by laypersons)

| This pilot trial is designed to determine whether PET/CT-guided radiotherapy dose escalation can improve local control while minimizing toxicity for the treatment of locally advanced nasopharyngeal carcinoma. One distinct advantage of PET/CT in radiotherapy planning is its potential to improve target identification, reducing intra-observer and inter-observer variability. We hypothesize that the use of PET/CT in treatment planning can improve dose-escalation radiotherapy for NPC which in turn can improve therapeutic efficacy while reducing toxicity. We prespecified our primary subgroup analysis on the basis of PET / CT positioning and SMART-IMRT. We also did prespeciﬁed secondary subgroup analyses based on sex, age, and c[linical stages](dict://key.0895DFE8DB67F9409DB285590D870EDD/clinical stages). For all subgroup analyses, we used the Kaplan-Meier method to calculate the actuarial rates of local control, DFS and OS. The χ2 test was used for comparing incidence rates and categorical variables and Student’s t-test was used for comparing the means of continuous variables, designated to be significant at p<0.05. PET-CT fusion may have significant impact on staging and radiotherapy treatment delineation in NPC. PET/CT-guided dose escalation radiotherapy appears to be well-tolerated. The SMART-IMRT technique to enhance BED of GTV, combined with concurrent chemotherapy, is completely feasible for local advanced NPC. |
| --- |

**8. Major Ethical Issues** (＜500 words, use language that can be understood by laypersons)

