**PART Ⅱ: STUDY DETAILS**

**9.** Scientific basis

| 9.1 | Background, current evidence and key references: | | |
| --- | --- | --- | --- |
|  | Nasopharyngeal carcinoma (NPC) differs from other head and neck malignancies in terms of its epidemiology, pathology, and treatment outcomes. It is endemic in China and is one of the major public health problems. Concurrent radiotherapy and chemotherapy is the primary treatment for patients with NPC. In recent years, with the development and application of comprehensive treatment and Intensity Modulated Radiation Therapy (IMRT) technology, the overall prognosis of nasopharyngeal carcinoma has been significantly improved, 5-year survival rate was 74.5% , 3 -year local control rate was 90%[2]. Despite such aggressive treatment, many patients with locally advanced NPC still develop locally recurrent disease [3].Since local control is directly related to patient’s morbidity and mortality in NPC, there is a strong requirement to develop a method for improving current treatments’ efficacy.  One strategy to improve local control is escalating the dose of radiotherapy. This is because local control has been shown to be directly related to the radiotherapy dose . Several techniques, including brachytherapy , stereotactic radiosurgery , and dose-painting intensity modulated radiotherapy (IMRT) , have been used to increase radiotherapy dose. However, due to the large number of critical anatomic structures near the nasopharynx, dose-escalation in NPC can also lead to increased toxicities . One of the more effective techniques is the simultaneous modulated accelerated radiation therapy (SMART) IMRT technique [10]. It delivers both accelerated radiotherapy and hypofractionated radiotherapy to the GTV. The main challenge for these treatments is to identify the appropriate tumor volume that could be received the high-dose radiotherapy. Conventional dose-escalation is conducted via using computed tomography (CT) to identify the gross tumor volume (GTV). However, recent progress in the field of ﬂuorine-18-ﬂuorode-oxyglucose positron emission tomography/computed tomography (18F-FDG-PET/CT)-adjuvant treatment planning allows more accurate tumor volume delineation ]. Thus, we hypothesize that of 18F-FDG-PET/CT-adjuvant treatment planning can improve dose-escalation radiotherapy for NPC, which in turn can improve therapeutic efficacy as well as reducing toxicity.  To identify this hypothesis, we compared the efficacy and toxicity of three treatments, including conventional chemoradiotherapy, CT-guided dose-escalation chemoradiotherapy and PET/CT guided dose-escalation chemoradiotherapy, in patients with locally advanced NPC via a randomized clinical trial in our department. PET-CT fusion may have significant impact on staging and radiotherapy treatment delineation in NPC. PET/CT-guided dose escalation radiotherapy appears to be well-tolerated. The SMART-IMRT technique to enhance BED of GTV, combined with concurrent chemotherapy, is completely feasible for local advanced NPC.  [1] Wei WI, Sham JS. Nasopharyngeal carcinoma. Lancet. Jun 11-17 2005;365(9476):2 041-2054.  [2] Lu H, Peng L, Yuan X, Hao Y, et al.Concurrent chemoradiotherapy in locally advanced nasopharyngeal carcinoma: a treatment paradigm also applicable to patients in Southeast Asia. Cancer Treat Rev. 2009, 35 (4):345-353.  [3] Wee J, Tan EH, Tai BC, et al. Randomized trial of radiotherapy versus concurrent chemoradiotherapy followed by adjuvant chemotherapy in patients with American Joint Committee on Cancer/International Union against cancer stage III and IV nasopharyngeal cancer of the endemic variety. J Clin Oncol. 2005;23(27):6730-6738.  [4] Marks JE, Bedwinek JM, Lee F, Purdy JA, Perez CA. Dose-response analysis for nasopharyngeal carcinoma: an historical perspective. Cancer. Sep 15 1982;50(6):1042-1050.  [5] Teo PM, Leung SF, Tung SY, et al. Dose-response relationship of nasopharyngeal carcinoma above conventional tumoricidal level: a study by the Hong Kong nasopharyngeal carcinoma study group (HKNPCSG). Radiotherapy and oncology : journal of the European Society for Therapeutic Radiology and Oncology. Apr 2006;79(1):27-33.  [6] Teo PM, Leung SF, Lee WY, Zee B. Intracavitary brachytherapy significantly enhances local control of early T-stage nasopharyngeal carcinoma: the existence of a dose-tumor-control relationship above conventional tumoricidal dose. International journal of radiation oncology, biology, physics. Jan 15 2000;46(2):445-458.  [7] Hara W, Loo BW, Jr., Goffinet DR, et al. Excellent local control with stereotactic radiotherapy boost after external beam radiotherapy in patients with nasopharyngeal carcinoma. International journal of radiation oncology, biology, physics. Jun 1 2008;71(2):393-400.  [8] Lin S, Pan J, Han L, et al. Nasopharyngeal carcinoma treated with reduced-volume intensity-modulated radiation therapy: report on the 3-year outcome of a prospective series. Int J Radiat Oncol Biol Phys. 2009; 75(4):1071-8.  [9] Ashamalla H, Guirgius A, Bieniek E, et al. The impact of positron emission tomography/computed tomography in edge delineation of gross tumor volume for head and neck cancers [J]. Int J Radiat Oncol Biol Phy, 2007, 68 (2):388-395.  [10] Butler EB, Teh BS, Grant WH, 3rd, et al. Smart (simultaneous modulated accelerated radiation therapy) boost: a new accelerated fractionation schedule for the treatment of head and neck cancer with intensity modulated radiotherapy. International journal of radiation oncology, biology, physics. Aug 1 1999;45(1):21-32.  [11] Madani I, Duthoy W, Derie C, et al. Positron emission tomography-guided, focal-dose escalation using intensity-modulated radiotherapy for head and neck cancer. International journal of radiation oncology, biology, physics. May 1 2007;68(1):126-135.  . | | |

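### The arm described as CT-guided dose escalation is tabled at the control arm's total dose and duration; if the table is what is delivered, no pair of arms isolates PET/CT guidance

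*Protocol*

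**What the plan says.** Section 9.1 of the Protocol names the three treatments as "conventional chemoradiotherapy, CT-guided dose-escalation chemoradiotherapy and PET/CT guided dose-escalation chemoradiotherapy". Of the SMART technique it says "It delivers both accelerated radiotherapy and hypofractionated radiotherapy to the GTV", and it gives the purpose as raising the BED of the gross tumour volume (GTV): "The SMART-IMRT technique to enhance BED of GTV, combined with concurrent chemotherapy".

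Section 12.3 is the only place that gives a dose for each arm. Its three rows read:

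- Article 1: "SMART-IMRT;PET/CT | | | 7 Week(s) | | 77Gy"
- Article 2: "SMART-IMRT; CT | | | 7 Week(s) | | 70Gy"
- Control: "Control | Radiotherapy | IMRT; CT | | | 7 Week(s) | | 70Gy"

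The rows share the same column structure, so the figures do not look like a reading error.

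On what the trial should show, section 7 (Brief Summary) says "We hypothesize that the use of PET/CT in treatment planning can improve dose-escalation radiotherapy for NPC", and section 9.1 repeats the idea. Section 7 also says "We prespecified our primary subgroup analysis on the basis of PET / CT positioning and SMART-IMRT". The title and the hypothesis field in section 9.3 put it differently: both set PET/CT-guided dose escalation against conventional treatment.

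**The concern.** An arm named for dose escalation should differ from control in some stated feature of dose or fractionation. In section 12.3 the CT-planned SMART arm does not. Its total dose and its number of weeks equal those of control, and nothing else about its delivery is given. Either the description or the table is incomplete or wrong.

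Two things are at stake. First, the protocol does not say clearly what one randomized arm receives. Second, the claim that PET/CT planning improves dose escalation calls for a comparison of PET/CT-planned with CT-planned escalation in which nothing else differs. The CT-planned SMART arm appears to be there for that purpose. If it has a lower dose than the PET/CT arm, it cannot serve it.

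**Working it through.** **Inputs.** Dose, duration, technique and planning image for each arm come from section 12.3; the arm descriptions come from section 9.1. Fraction number and α/β ratio are not in the Protocol and are assumed where used.

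**Step 1: description against table.**

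| Arm | Name in 9.1 | Image | Technique | Total dose | Weeks | Gy per week |
|---|---|---|---|---|---|---|
| 1 | escalated | PET/CT | SMART-IMRT | 77 Gy | 7 | 77/7 = 11.0 |
| 2 | escalated | CT | SMART-IMRT | 70 Gy | 7 | 70/7 = 10.0 |
| Control | conventional | CT | IMRT | 70 Gy | 7 | 70/7 = 10.0 |

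- Arm 2 minus control: 70 − 70 = 0 Gy, ratio 1.00, same number of weeks.
- Arm 1 minus arm 2: 77 − 70 = 7 Gy, ratio 77/70 = 1.10.

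As tabled, arm 2 has no higher total dose than control and no shorter course. The second point leaves the word accelerated in 9.1 without support.

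**Step 2: what each pair of arms compares, if the table is what is delivered.**

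- Arm 1 against arm 2: imaging and total dose differ.
- Arm 1 against control: imaging, technique and total dose differ.
- Arm 2 against control: technique differs, with the same imaging and the same total dose.

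Code the arms as (PET/CT, SMART, 77 Gy): arm 1 is (1, 1, 1), arm 2 is (0, 1, 0) and control is (0, 0, 0). The columns for PET/CT and 77 Gy are identical. No pairwise test separates them, and no model fitted to these arms can. An analysis by PET/CT positioning, as section 7 plans, is therefore also an analysis by 77 Gy against 70 Gy.

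**Step 3: could unstated fractionation remove the difference between the SMART arms?** Use BED = D × (1 + d/(α/β)), where D is total dose and d is dose per fraction. Assume α/β = 10 and 28 to 35 fractions.

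- 70 Gy in 35 fractions: 70 × (1 + 2.0/10) = 84.0
- 70 Gy in 28 fractions: 70 × (1 + 2.5/10) = 87.5
- 77 Gy in 35 fractions: 77 × (1 + 2.2/10) = 93.9
- 77 Gy in 28 fractions: 77 × (1 + 2.75/10) = 98.2

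This cuts two ways. Arm 2 could have a somewhat higher BED than control (up to 87.5 against 84.0) at the same total dose. But over the assumed range the 70 Gy figures (84.0 to 87.5) never reach the 77 Gy figures (93.9 to 98.2). With α/β = 3 the ranges are 116.7 to 128.3 and 133.5 to 147.6, again without overlap. These figures only illustrate the point; they do not describe what the trial gives.

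**The case against.** Four points on the other side deserve weight.

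1. **Equal total dose is not proof of no escalation.** A reader might infer from the table that arm 2 is simply the control treatment. The documents do not support that. BED depends on dose per fraction as well as total dose, section 9.1 calls SMART hypofractionated, and the table has one dosage field and one duration field with no target volume named. This stands. What remains is that the Protocol does not document any escalation in arm 2.

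2. **The confounding is conditional.** A reader might conclude that the PET/CT effect is confounded with dose, without qualification. That holds only if section 12.3 is what patients receive. If the 70 Gy entry for arm 2 is a slip and both SMART arms have the same dose, the confounding goes and only the contradiction in the document remains. The documents do not show which is the case. This stands.

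3. **The formal comparison is of a package.** The title and section 9.3 set PET/CT-guided escalation against conventional treatment. Arm 1 against control answers that whatever arm 2 receives, and better delineation that permits a higher dose can fairly be seen as one intervention. This stands for that comparison. It does not explain why arm 2 is called dose escalation, nor does it cover the wording of sections 7 and 9.1 or the planned analysis by PET/CT positioning and SMART-IMRT.

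4. **Differences between sites.** A reader might fear that different sites would follow different passages. Section 10.4 places all 90 patients at the applying site, so that inference fails. The ambiguity concerns one treating team.

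**Conclusion.** The point holds as an inconsistency that must be resolved. Section 9.1 calls the CT-planned SMART arm dose-escalated; section 12.3 gives it 0 Gy more than control over the same 7 weeks, and nothing in the Protocol shows another route to escalation.

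On the assumption that section 12.3 is what is delivered, the two SMART arms differ by 7 Gy (10%) as well as in imaging, and no pair of arms isolates PET/CT guidance. Confidence is high for the inconsistency and conditional for the confounding. The comparison of arm 1 with control remains valid as the joint effect of imaging, technique and dose, so it would be wrong to say that the trial cannot answer the question in its title.

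**What to change.** The responsible clinicians should reconcile sections 9.1 and 12.3 so that the arm descriptions and the dose and duration entries agree, and should state the fractionation and target volume on which any claim of escalation in the CT-planned arm rests. This review takes no position on which passage is right.

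The Protocol should then state in a sentence or two what each pairwise contrast estimates. If arms 1 and 2 do differ in dose, it should say that their difference is the joint effect of PET/CT planning and dose and will not be attributed to PET/CT alone, and it should read the analysis by PET/CT positioning in section 7 in the same way.

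The cost is a correction to one table or one paragraph and, if the doses differ, a narrower conclusion about PET/CT. The sample size and randomization need not change on this account.

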**10. Study subjects**

| 10.1 | Inclusion criteria: |
| --- | --- |
| Patients with previously untreated Stages III and IVA (AJCC 6th Edition) of locally advanced NPC, and histologically confirmed NPC by biopsy, no evidence of distant metastasis, Karnofsky performance status≥70, and good bone marrow, liver and kidney function (white blood cell count ≥ 4.0×109/L, platelets ≥ 100×109/L, albumin ≥30 g/L, creatinine ≤100μmol/L). Ages eligible for study: 18 yeas to 70 years. Patients those with a prior (within 5 years) or synchronous malignancy were excluded. |
| 10.2 | Exclusion criteria: |
| There was evidence of distant metastases, previous malignancy or other concomitant malignant disease, pregnant or lactating, nasopharyngeal radiotherapy history, patients withdrew during treatment or doctor and other factors caused by violation of the study protocol. |
| 10.3 | Sample-size and rationale for calculation: |
| Sample-size= 90 ﹡  Based on the following rationale: To detect 3-year local progression-free survival (LPF） with a two-sided 5% significance level and a power of 80%, a sample size of 30 patients per group was necessary, given an anticipated dropout rate of 10%. |
| 10.4 | Number of subjects to be recruited locally in relation to this application: |
| n= 90 ﹡in applying site. |
| 10.5 | How will subjects to be identified and recruited? |
| We will publish the recruitment information of clinical trials on the website of Xuzhou Medical College Hospital (***http://www.jsxyfy.com/***). According to the specific inclusion criteria and exclusion criteria rigorous screening patients. |

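### The only stratification factor in section 12.7 has no defined levels and no evident variation among eligible patients, so stage is left unbalanced in arms of 30

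*Protocol*

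**What the plan says.** Protocol section 12.7 describes the allocation: "Block randomisation was by a computer generated random number list prepared by an investigator with no clinical involvement in the trial". The next sentence gives the only stratification factor in the document: "We stratified by admission for an oncology related procedure". It defines no levels for the factor and no block size.

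Section 10.1 sets the population: "Patients with previously untreated Stages III and IVA (AJCC 6th Edition) of locally advanced NPC, and histologically confirmed NPC by biopsy". Section 9.1 lists the three arms: "conventional chemoradiotherapy, CT-guided dose-escalation chemoradiotherapy and PET/CT guided dose-escalation chemoradiotherapy, in patients with locally advanced NPC". Section 7 names clinical stage, together with sex and age, as a basis for secondary subgroup analyses.

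On size, section 10.3 says "a sample size of 30 patients per group was necessary, given an anticipated dropout rate of 10" percent, and section 10.4 has all 90 patients recruited at the applying site.

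**The concern.** A stratification factor helps only if it takes different values among the randomised patients and is related to outcome. Here every patient has confirmed nasopharyngeal carcinoma and enters for chemoradiotherapy. On its plain wording the factor therefore puts everyone in the same stratum, and the blocks balance the number of patients per arm and nothing else.

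Stage has exactly two eligible levels, must be known to judge eligibility, and is already of interest to the investigators, yet it is left to chance. With 30 patients per arm, a visible stage difference between arms is common. It would make the result for local progression-free survival (LPF) harder to read and less precise.

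**Working it through.** **1. Does the factor vary?** Section 12.7 stratifies by an oncology-related admission. Section 10.1 requires untreated, histologically proven stage III or IVA disease. Section 9.1 assigns chemoradiotherapy, an oncology treatment, to every arm. Read together, these give no second level that an eligible patient could occupy. This is an inference, because the levels are not written down.

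**2. Arm size.** 3 × 30 = 90, which agrees with section 10.4. Allowing for 10% dropout leaves 30 × 0.90 = 27 evaluable per arm. The figure of 30 cannot be re-derived, because section 10.3 gives neither response rates nor a hazard ratio. The present point uses 30 only as the arm size.

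**3. Chance imbalance in stage when stage is not stratified.** The protocol does not give the share p in stage IVA; 30% to 70% is assumed. For two arms of 30, the standard deviation of the difference in stage IVA share is √(2p(1 − p)/30). At p = 0.5 this is √(0.5/30) = 0.129, or 12.9 points.

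A difference of 20 points is 6 patients. At p = 0.5 the difference in counts has standard deviation √(60 × 0.25) = 3.87. With a continuity correction, z = 5.5/3.87 = 1.42, and the two-sided probability is about 0.16. Simulation with fixed arm sizes and a fixed stage total (200,000 draws) gives:

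| Stage IVA share (assumed) | SD, points | Given pair, ≥10 points | Given pair, ≥20 points | Some pair of three, ≥10 points | Some pair of three, ≥20 points |
|---|---|---|---|---|---|
| 30% | 11.8 | 48.5% | 12.2% | 73.8% | 26.3% |
| 40% | 12.6 | 51.1% | 14.7% | 76.5% | 30.9% |
| 50% | 12.9 | 52.0% | 15.8% | 77.4% | 32.5% |
| 60% | 12.6 | 51.4% | 14.8% | 76.7% | 31.0% |
| 70% | 11.8 | 48.4% | 12.2% | 73.8% | 26.3% |

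Treating the arms as independent binomials gives nearly the same 20-point figures (15.5% and 33.0% at p = 0.5).

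**4. The same 90 patients with blocks run within stage.** Over 20,000 simulated trials at each of p = 0.3, 0.5 and 0.7, the largest stage difference between any two arms was 3.3 points with blocks of 3 (1/30) and 6.7 points with blocks of 6 (2/30). No trial reached 10 points.

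**5. What an imbalance does to LPF.** The protocol gives no LPF by stage, so this step is illustrative. It borrows the one background figure, 90% local control at 3 years (section 9.1), which is not stated to apply to stage III–IVA patients.

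- The standard error of a difference between two arms of 30 is √(2 × 0.9 × 0.1/30) = 0.077, or 7.7 points.
- With half the patients in stage IVA, an overall 90% allows a stage gap of at most 20 points (100% versus 80%). A 20-point imbalance then shifts the LPF difference by 0.20 × 0.20 = 4 points. With a 10-point gap the shift is 2 points.
- Stage imbalance then accounts for 0.0167 × 0.20² / 0.006 = 11% of the variance of the difference at the 20-point gap, and 0.0167 × 0.10² / 0.006 = 3% at the 10-point gap.
- A smaller stage IVA share allows a wider gap. At 30%, 0.7 × 100% + 0.3 × 66.7% = 90%, a gap of 33.3 points, and the shift is 0.20 × 33.3 = 6.7 points, still below the standard error.

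**The case against.** Several counter-arguments have force.

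*The one-level reading is an inference.* A reader might conclude that every eligible patient certainly shares the factor. The text does not establish that: no levels are given, and the factor could have been meant as inpatient versus outpatient at entry. This stands, so the point is limited to an undefined factor with no evident variation. Under the alternative reading stage would still be unbalanced and section 12.7 would still need its levels stated.

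*The consequence is modest.* A reader might infer that a stage imbalance would create or hide a treatment effect, or that the randomisation is invalid. Neither is supported. Randomisation without useful strata is still valid, and chance imbalance is part of the error that the test already allows for. Nor does the protocol state an LPF rate or an event count on which a claim of very few events could rest.

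*Simple blocking with later adjustment is a legitimate choice in a 90-patient pilot.* That is true, and covariate adjustment may sit in an analysis plan that is not shown. But the protocol did not choose simple blocking. It states a stratification, and the one stated does no visible work.

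*Stage is not singled out as prognostic.* Section 7 lists it on a level with sex and age. That stands. The case for stage is that it has two eligible levels, is known at entry and is already a planned analysis factor.

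*The text is in the past tense.* If allocation is already complete, a new list is no remedy, and a fallback is needed.

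**Conclusion.** The point holds in a limited form. Section 12.7 states a stratification factor without levels that, as worded, shows no evident variation in this population and so does not protect against stage imbalance. With 30 per arm, a stage difference of 20 points or more would occur in about one trial in six to eight for a given pair of arms, and in about one in three to four for some pair. These figures rest on an assumed stage IVA share of 30% to 70% and change little across that range.

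The cost is to precision and to the credibility of a single small trial. In the illustration at 90% control with half the patients in stage IVA, a 20-point imbalance moves the LPF difference by at most 4 points against a standard error of 7.7. A lower control rate or a smaller stage IVA share would allow more. The correction is worth making because it is cheap.

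**What to change.** In section 12.7, replace the present factor with AJCC stage (III versus IVA) and use permuted blocks within the two strata. Take stage as recorded at eligibility, before randomisation, and do not revise it from the planning PET/CT. The protocol itself expects PET/CT to affect staging (sections 7, 9.1 and 15), and section 12.3 lists it for one arm only, so a revised stage would be measured differently between arms.

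Carry stage into whichever primary LPF comparison is specified. Section 13 names Kaplan-Meier estimates, the χ² test and the t-test, so the wording should not presuppose a particular survival test.

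If allocation has already been done, report the factor and levels actually used, and adjust the primary LPF comparison for stage.

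Cost: one new two-stratum list and a few incomplete blocks. No extra patients are needed, and two strata are manageable for 90 patients at one site.
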